#### Quality Assurance, Monitoring, and Safety

Only the study investigators will monitor the study. No interim analysis is planned because the intervention is not expected to cause harm. Each completed study questionnaire will be reviewed for completeness upon participant submission. Participants who score in the clinical range on the EPDS (≥13 for mothers, ≥9 for fathers) will be flagged and encouraged to follow-up with their primary health care practitioner. Parents will be referred to the appropriate health care provider(s) or agencies if they experience severe distress at any point during the study.

The study protocol may be stopped or changed if the following safety concerns arise from either participants’ completed study questionnaires or the home visits: (1) concern for a participant’s potential to cause harm to self or others; (2) concerns of abuse or neglect of participants or their child; or (3) concern for the home visitor’s physical safety.

There are no known physical risks to participants taking part in this study. Participants may feel uneasy being video-recorded while playing with their baby, completing questionnaires, or answering questions during the interview. No audit is planned for this study.

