#### Discontinuing or Modifying Allocated Interventions

Given the brevity of the intervention, situations that require discontinuing or modifying the allocated intervention are expected to be rare. In cases of family illness or acute parental mental or physical health concerns, the home visit will be either rescheduled or discontinued altogether, according to family preference. Families who discontinue will be offered a listing of local community health services to which they can self-refer.

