Expanded Brief Infant Sleep Questionnaire [BISQ; (48, 53)]	32-item questionnaire of infant sleep patterns, sleep ecology, and caregiver perceptions; responses include numerical (time, frequency), categorical (sleep location, bedtime activities), and ordinal rankings (how much of a problem is your baby’s sleep). No composite score is calculated. High 3-week test–retest reliability for sleep duration and wakefulness, night wakings, sleep-onset time, and settling time (0.82–0.95; 48). Used to assess sleep interventions for infants 6–36 months with a parent-identified sleep problem and detect significant short- and long-term improvements in the number of infant night wakings and sleep latency (49, 55, 56). Used in an internet sample (*N* = 4,505) of Canadian and United States parents of infants aged 0–36 months (53) and an international sample (*N* = 29,287) of parent of infants aged 0–36 months (57). Night wakings correlated with actigraphy, *r* = 0.42, and daily logs, *r* = 0.83 (48). Frequency of night wakings accounted for 13.27% of variance in parental perceptions of severity of sleep problems (53). Differentiated between clinical and control infants with two BISQ items, frequency of night wakings and nocturnal sleep duration, with assignment of cases to the correct group 85% of the time (48). Average completion time is 6.21 min (53)

**Table 3 T3:** Covariate measures.

Measure	Description
PCITS (34)	73-item binary measure of parent–child interactions on 4 parent (sensitivity to cues, response to distress, social-emotional, and cognitive growth fostering) and 2 child (clarity of cues and responsiveness to caregiver) subscales. Higher scores indicate higher quality interactions. Internal consistency for mothers, α = 0.53–0.87 (34) and fathers, α = 0.64–0.82 (58). Test–retest reliability (1 and 12 months) of 0.85 for caregiver and 0.55 for infant subscales (34). Concurrent validity with Home Observation Measure of the Environment scale (59). Predicts attachment, cognitive and language abilities (34, 60). Play session typically lasts 3–5 min
EPDS (61)	10-item measure of symptoms of depression, anxiety, and suicidal thoughts. Higher scores indicate more depressive symptoms. In mothers, correlated with Beck Depression Inventory second version, 0.82 (62). In fathers, EPDS was correlated with Center for Epidemiologic Studies Depression Scale, 0.62 (63). Internal reliability in mothers, α = 0.53–0.87 (62) and fathers, α = 0.87 (63); takes 3–5 min

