**Assessments**						
*Expanded BISQ*		X			X	
*PCITS*				X	X	
*EPDS*		X			X	
*IBQ-R very short form*		X			X	
*MCISQ*		X			X	
*DAS-4*		X			X	
*PSOC*		X			X	
*Interview*						X

*BISQ, Brief Infant Sleep Questionnaire; PCITS, Parent–Child Interaction Teaching Scale; EPDS, Edinburgh Postnatal Depression Scale; IBQ-R, Infant Behavior Questionnaire—Revised; MCISQ, Maternal Cognitions about Infant Sleep Questionnaire; DAS-4, Brief version of the Dyadic Adjustment Scale; PSOC, Parental Sense of Competence*.

Online study questionnaires, hosted on Qualtrics, will be used to collect the majority of data on outcomes and covariates at baseline, when the infant is aged 5 months, and at outcome, when the infant is aged 7 months. Qualtrics is a recognized and secure electronic survey system that houses data on secure Canadian servers. Parents (mothers and fathers) in both groups will each complete baseline questionnaires in the 7 days prior to the initial home visit. A link to the baseline questionnaires will be emailed to parents 5–7 days before the home visit, and an email reminder encouraging parents to complete the questionnaires prior to the home visit will be sent if necessary.

The first home visit will occur when the infant is 5 months old (±2 weeks), at a time that is convenient to the family. [name] and colleagues (38) have demonstrated 5 months of age is a feasible time-point to begin a video self-modeled intervention. Scheduling the home visit when the infant is 5 months of age will allow sufficient time between referral to the study at the 4-month well-child clinic visit and scheduling of the first home visit. Scheduling the home visits within a 2-week window of 5 months provides a realistic timeframe to schedule visits based on availability of both parents, as well as being able to re-schedule visits if there are unanticipated events (i.e., infant illness). This narrow window minimizes maturation bias due to the rapid developmental changes that occur in infants at this age.

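### The EPDS safety flag uses the total score alone, so it misses suicidal thoughts reported below the cut-off, and no other provision links that answer to a referral

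*Protocol article*

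**What the plan says.** Table 3 of the protocol article (Measures) describes the EPDS as a "10-item measure of symptoms of depression, anxiety, and suicidal thoughts". Under Data Collection and Management, both parents complete it online shortly before each home visit. For baseline: "Parents (mothers and fathers) in both groups will each complete baseline questionnaires in the 7 days prior to the initial home visit". The same arrangement applies before the 7-month visit.

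The section Quality Assurance, Monitoring, and Safety then sets out what happens to the answers:

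- Review on receipt: "Each completed study questionnaire will be reviewed for completeness upon participant submission".
- EPDS flag: "Participants who score in the clinical range on the EPDS (≥13 for mothers, ≥9 for fathers) will be flagged and encouraged to follow-up with" a primary care practitioner.
- Referral: "Parents will be referred to the appropriate health care provider(s) or agencies if they experience severe distress at any point during the study".
- Safety concerns: "The study protocol may be stopped or changed if the following safety concerns arise from either participants’ completed study questionnaires or the home visits". Item (1) of that list is "concern for a participant’s potential to cause harm to self or others".

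The section Discontinuing or Modifying Allocated Interventions adds: "In cases of family illness or acute parental mental or physical health concerns, the home visit will be either rescheduled or discontinued altogether". Families who discontinue receive a list of services to which they can refer themselves.

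**The concern.** The instrument asks about suicidal thoughts, but the rule that acts on it looks at the total. A total cannot distinguish a parent who endorses that item from one who reaches the same score on other items. A positive answer that comes with few other symptoms therefore passes the flag, although the trial holds the answer on file.

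What is at stake is participant safety. The Introduction notes that infant sleep disturbance is associated with maternal depression and anxiety and with parental guilt and helplessness, so the item is relevant to the families recruited. Every EPDS form precedes a planned home visit by about a week or less, so there is a contact at which an alert could be acted on. The estimand, sample size and error control are not involved.

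**Working it through.** **Inputs.** From Table 3: 10 items, higher scores meaning more symptoms, suicidal thoughts covered. From Quality Assurance, Monitoring, and Safety: cut-offs of 13 (mothers) and 9 (fathers). From Trial Status: 54 families enrolled, 61 expected to be needed for 60 complete. The article does not give the scoring range of an item or the frequency of positive answers. There is no stated figure to reproduce.

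**1. Can the item alone trigger the flag?** The highest unflagged totals are 13 − 1 = 12 (mother) and 9 − 1 = 8 (father). Suppose the ten items are scored alike from 0 to a maximum m.

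- A total of 13 must be reachable. With m = 1 the highest total is 10 × 1 = 10, below 13, so m is at least 2.
- The suicidal-thoughts item alone reaches a cut-off only if m is at least 9 (father) or at least 13 (mother).
- So for any m from 2 to 8, even the highest answer on this item reaches neither cut-off by itself.

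**2. How far can the flag miss?** Assume scoring of 0 to 3. The other nine items can then total at most 9 × 3 = 27. A parent stays unflagged if those nine items sum to no more than the highest unflagged total minus the answer:

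| Answer on the item | Mother: other nine items up to | Father: other nine items up to |
|---|---|---|
| 1 | 12 − 1 = 11 | 8 − 1 = 7 |
| 2 | 12 − 2 = 10 | 8 − 2 = 6 |
| 3 | 12 − 3 = 9 | 8 − 3 = 5 |

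**3. Does another provision catch the answer?**

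| Provision | What triggers it | Stated consequence | What is missing |
|---|---|---|---|
| Review on submission | Every form | Check for completeness | No review of content is stated |
| Harm to self | Concern arising from questionnaires or visits, no score threshold | The study protocol may be stopped or changed | No referral of the parent; no answer named |
| Severe distress | Severe distress at any time | Referral | No questionnaire answer named as trigger |
| Acute mental health concern | Acute concern | Visit rescheduled or discontinued; self-referral list if discontinued | No EPDS answer named; no active referral |

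The harm-to-self provision comes closest. The EPDS is the only listed questionnaire described as covering suicidal thoughts, so the clause most naturally points to it. Its stated consequence, however, concerns the study protocol. The referral exists, but no trigger runs from this item to it.

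**4. How many forms could a change still reach?** These are forms, not missed cases.

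- Families still to enrol: 61 − 54 = 7. Forms: 7 × 2 parents × 2 time points = 28.
- Families expected to be incomplete: 61 − 60 = 1. If it is among the seven and misses only its 7-month forms: 28 − 2 = 26. If it returns none: 28 − 4 = 24.
- Outstanding 7-month forms of enrolled families: between 0 and 54 × 2 = 108, number not given. Table 4 places enrolment before baseline, so some baseline forms may also be due, number not given. No overall total can be stated.

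**The case against.** The strongest reply is that the safety section should be read as a whole. It has a harm-to-self provision that is fed by questionnaires and has no score threshold, close to a referral provision that is not limited to any source or score. Read together, they would let staff refer a parent whose answer raised concern. The listed safety concerns also relate to individual participants, families or the visitor, so the clause about stopping or changing the protocol may be meant at family level. Computing EPDS scores requires someone to look at the content, so the review need not be confined to completeness. This much stands: the plan is not silent on self-harm, and an attentive reader of the forms could act. It does not close the gap, because acting would rest on discretion, whereas the section otherwise sets a defined EPDS trigger. No sentence makes this answer a reason for referral.

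A second reply is that a journal article condenses the protocol, and the full document or ethics submission may contain an item-level step. That is possible and limits confidence. But the article does not leave EPDS handling to another document: it states the rule, both cut-offs and the action. The rule as stated is too narrow.

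Third, the size is soft. The frequency of positive answers is unknown, 0 to 3 scoring is assumed, and the form counts are not counts of missed parents. The one expected incomplete family may already be among those enrolled, which would favour 28. The article also expects attrition after the first visit, which makes 24 less likely. These points are fair. They bear on the size and leave the gap itself unaffected.

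**Conclusion.** The concern holds. The EPDS flag is a total-score rule, a positive suicidal-thoughts answer below 13 (mother) or 9 (father) passes it, and none of the other safety provisions connects that answer to a referral. That the item alone cannot trigger the flag holds for any common item maximum from 2 to 8; the specific margins assume 0 to 3 scoring. The number of parents affected cannot be estimated from the article. Confidence is medium, because an item-level procedure may exist in a document not shown. The point should be addressed as a safety improvement; it is not a flaw in the design or analysis of the comparison.

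**What to change.** At both 5 and 7 months, flag any non-zero answer on the EPDS suicidal-thoughts item on submission, whatever the total. This can be done by adding the item to the existing review on receipt or by an alert in the online survey. State that such an answer counts under the harm-to-self provision and leads to the referral to a health care provider or agency already described in Quality Assurance, Monitoring, and Safety. Keep the total-score flag unchanged. Response time and clinical action are for the investigators and the ethics board to set.

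The cost is one item check or alert, a short ethics amendment and a few more alerts to handle. No new measure or visit is needed, and randomization, sample size and analysis stay as they are. With 54 families enrolled, the change comes too late for forms already submitted.

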## Anticipated Results

### Phase 1 Quantitative Analysis

Quantitative data will be analyzed using IBM SPSS Statistics 24.0 software. Data will be examined for frequency and patterns of missing data. If less than 20% of the data are missing, and if missing at random or completely at random, missing values will be imputed using multiple imputation (80). Descriptive statistics (means, SDs, frequencies, and percentages) will be used to describe the sample, and correlations between variables will be examined to identify potential covariates. Using the “intent to treat” principle, a RM-ANOVA will be used to detect differences between groups over time in mother and father reports of infant sleep patterns that are measured as continuous variables (night wakings, nocturnal wakefulness, and longest period of consolidated nighttime sleep). To control for Type I error that may result from multiple hypothesis testing, we will apply a Bonferroni correction during the analyses. Ordinal level infant sleep variables (sleep latency and parental perception of problematic sleep) will be analyzed using a Wilcoxon signed-rank test. If there are statistically significant differences between groups on the primary outcome, sub-analyses will identify which covariates have significant effects. Parent–child interactions scores for both mothers and fathers will be compared to normed scores available from the NCAST database.

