**Method and analysis:**

An explanatory sequential mixed methods design will be used. In the quantitative phase, a randomized controlled trial and RM-ANOVA will compare night wakings in infants whose parents receive Play2Sleep versus standard public health nursing information. Sixty English-speaking families (mothers and fathers) of full-term, healthy, singleton, 5-month-old infants who perceive that their infant has sleep disturbances will be recruited. The primary outcome measure will be change in the number of night wakings reported by parents. The qualitative component will use thematic analysis of family interviews to describe parental perceptions and experiences of infant sleep. Mixed methods integration will use qualitative findings to explain quantitative results.

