The proposed nursing theory described by [name] and [name] (41) forms the theoretical underpinnings of this study. Informed by Bronfenbrenner’s ecological theory (42, 43) and Barnard’s Model of parent–child interactions (44), [name] and [name] guide nurses to consider parental knowledge and beliefs about infant sleep with the family’s synchrony, not only relating to sleep but also the family’s ability to engage in effective parent–infant interactions. As such, nurses are encouraged to enhance parental knowledge related to infant sleep, as well as the underlying foundational familial interactions that support parental ability to apply knowledge relating to infant sleep during daily and foundational parent–infant interactions. Play2Sleep is an intervention that uses personalized feedback of structured parent–infant play sessions. This approach could help address broader parenting difficulties that may underlie infant sleep disturbances by enhancing parental ability to identify and respond appropriately to their infant’s specific sleep-related and social cues. This study extends previous self-modeled, video-recorded interaction guidance interventions and aims to evaluate Play2Sleep to improve infant sleep. This protocol was prepared in accordance with the SPIRIT guidelines (45), as well as the TIDieR checklist and guide (46) for reporting of interventions.

The overarching mixed methods research aim is to understand how parental perceptions of family experiences, processes, and contexts related to infant sleep explain the effectiveness of Play2Sleep. The objective of the quantitative phase is to compare the effect on infant sleep of one dose of Play2Sleep delivered during home visits with mothers and fathers of 5-month-old infants with sleep disturbances against standard infant sleep education only. The primary hypothesis is that Play2Sleep will decrease the number of night wakings at the age of 7 months. The objective of the qualitative phase is to describe parental perceptions of family experiences, processes, and contexts related to Play2Sleep and infant sleep.

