## Materials and Equipment

### Study Design

This study will employ a mixed methods, explanatory sequential design to evaluate the Play2Sleep intervention, with priority given to the quantitative phase (Figure 1). Phase 1 is a single center, prospective, randomized, controlled, parallel group, two arm, superiority trial with a 1:1 allocation ratio (ClinicalTrials.gov, identifier NCT02742155). Baseline data collection and intervention will occur when the infant is 5 months of age (±2 weeks), with outcomes measured when the infant is 7 months of age (±2 weeks). During Phase 2, interviews will be conducted with a subset of participating families (mothers and fathers together) about their perceptions and experiences related to their infant’s sleep. The interviews will occur after the outcome home visit takes place, and analyzed using thematic analysis. Phase 3, the integration phase, will focus on explaining the quantitative results from Phase 1 using the qualitative findings from Phase 2.

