### Participants

The study will take place in a large urban center in Western Canada (Calgary, AB, Canada). Public health nurses will introduce potential participants to the study during 4-month well-baby clinics at eight urban-zone local community health centers. In addition to recruitment posters and postcards placed at each of the community health centers, researchers will use a social media campaign to promote the study on Facebook and Kijiji. At the community health centers, interested families will receive a card with a brief description of the study and public health nurses will request written permission from the parents to be contacted by the researcher. Upon contact with interested families, the researcher will follow a telephone script to (1) screen parents for eligibility, (2) obtain verbal consent from both parents to participate, (3) collect contact information, and (4) schedule the first home visit. Parents who are ineligible for the study will be offered standard public health information on infant sleep and provided with a list of community resources to which they can self-refer.

Participants (mothers and fathers) will be eligible if they meet the following inclusion criteria: (1) are cohabiting mothers and fathers of full-term, healthy, singleton, 4-month-old infants; (2) are first-time parents; (3) are able to read, write, and speak English; (4) perceive that their infant has sleep disturbances; (5) have an infant who has greater than 3 night wakings per night and/or is awake greater than 60 min during the night, and/or has less than 9 h total day and nighttime sleep. Infants meeting one or more of these three objective sleep criteria were considered to be poor sleepers by Sadeh (48) in the development of the original Brief Infant Sleep Questionnaire (BISQ). Participants will be excluded if there is a known or suspected medical or physiological cause of sleep disturbance in either parent or their infant.

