### Sample Size

The effect size for the sample size calculation for the quantitative phase was estimated from research that examined brief sleep interventions with the number of night wakings as the primary outcome. A study of a brief internet intervention for families of young children up to age 3 years that provided a customized sleep program, with and without a standardized bedtime routine, found relatively large effect sizes (partial eta squared) of 0.442 and 0.441, respectively (49). In a narrower age group of infants 6–12 months, Hall and colleagues (50) found an effect size (Cohen’s *d*) of 0.64 for an intervention that included a 2-h teaching session and telephone support for parents. An *a priori* analysis was conducted in G*Power for repeated measures ANOVA, between factors (51). This calculation determined that a total sample size of 60 mother–father–infant triads (30 families in each group) would detect an effect size of 0.32 with a power of 0.80 at a 0.05 level of significance (Figure 2), which is below the effect size of the aforementioned studies (49, 50). Recruitment will be ongoing until complete data are collected from 60 families. Based on previous studies (37, 39), attrition is estimated to be very low (less than 5%) after the initial home visit. Figure 3 shows the proposed Consolidated Standards of Reporting Trials flow diagram.

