An automated randomization service (77) will generate the randomization sequence to allocate families to either the experimental or comparison group. Allocation concealment will be achieved because the randomization code will not be requested until the family enrolls in the study and parents complete the baseline questionnaire. After participants have completed the baseline questionnaire and immediately before the initial home visit, the home visitor will submit an online form requesting treatment allocation. A copy of the allocation will be emailed to the home visitor and stored in the study’s online Sealed Envelope Ltd. account.

At the start of the first home visit, participants will affirm their verbal consent (provided during the eligibility screening phone call) by providing written consent. After establishing initial rapport with the parents, the home visitor will ask each parent (mother and father) to teach their infant a unique age-appropriate play task, which is video-recorded by the home visitor to be coded later using the PCITS coding scheme (34). As per the PCITS manual, the video-taped structured teaching and play sequence lasts no longer than 10 min, typically spanning a 3- to 5-min timeframe (34). The order of the video-recordings will alternate between the mother and father to prevent ordering bias. Following the video-recorded structured play session, the home visitor will deliver either the Play2Sleep or comparison intervention. At the conclusion of the home visit, the home visitor will offer to schedule the outcome home visit.

The outcome home visit will occur when the infant is aged 7 months (±2 weeks). Seven months was selected because parents need time to practice and solidify new interaction patterns to translate into measurable effects on infant sleep patterns. Parents (mothers and fathers) in both groups will each complete outcome questionnaires in the 7 days prior to the second (outcome) home visit. During the outcome home visit, parents in both the experimental and comparison groups will again engage their infant in a different play task that is video-recorded for later coding. All families will be offered a listing of local infant sleep-related resources and services. Once data collection is completed, data will be downloaded, backed-up, and deleted from the Qualtrics account.

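### The planned RM-ANOVA of night wakings is a valid test on change, but adjusting for baseline would be more efficient at almost no cost

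*Protocol article*

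**What the plan says.** The Phase 1 Quantitative Analysis section fixes the method: under intention to treat, "a RM-ANOVA will be used to detect differences between groups over time". It covers the reports of both parents on night wakings, nocturnal wakefulness and the longest sleep period.

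The outcome is worded in two ways. The Abstract says "The primary outcome measure will be change in the number of night wakings reported by parents". The Introduction says "The primary hypothesis is that Play2Sleep will decrease the number of night wakings at the age of 7 months".

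There are two measurement times: a 5-month baseline, and a second round "with outcomes measured when the infant is 7 months of age" (Study Design). The order of baseline and allocation is clear from Data Collection and Management: "After participants have completed the baseline questionnaire and immediately before the initial home visit, the home visitor will submit an online form requesting treatment allocation". Treatment therefore cannot affect the baseline value.

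Baseline night wakings is not named as a covariate. Candidate covariates are to be found from observed correlations, and their effects are examined in sub-analyses only if the primary comparison is significant.

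**The concern.** RM-ANOVA on a baseline and a single follow-up treats the baseline as a second response. The group-by-time contrast then subtracts the whole baseline value from each family's 7-month value, even though the two are imperfectly correlated. This has two consequences:

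- Baseline noise is carried into the treatment estimate, so its standard error is larger than it need be.
- If the arms differ at baseline by chance, subtracting the full difference removes more than the part expected to persist to 7 months.

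With 30 families per arm, both can matter. The covariate that would deal with them is already being collected before randomisation.

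**Working it through.** **The plan's own figure.** The Sample Size section uses the G*Power between-factors routine: f = 0.32, 60 families, power 0.80, alpha 0.05. The article states neither the number of measurements m nor the correlation ρ. Assume m = 2 and ρ = 0.5:

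λ = f²·N·m / (1 + (m − 1)ρ) = 0.1024 × 60 × 2 / 1.5 = 8.192

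On 1 and 58 df this gives power 0.804. N = 58 gives 0.790, so 60 is reproduced. That routine is for the between-group main effect, which averages baseline and outcome. The comparison below concerns the group-by-time contrast, which is the natural reading of differences between groups over time and matches the change outcome.

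**Equivalence.** In a simulated two-time-point data set with 30 per arm, the group-by-time F and the squared t on change were both 5.794. The identity is exact.

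**Variance.** Let SD be the standard deviation, assumed equal at both ages. The variance of the treatment estimate is v × SD² × (2/30), where

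- change score: v = 2(1 − ρ)
- ANCOVA: v = 1 − ρ²
- ratio, ANCOVA to change: (1 + ρ)/2

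**Power.** λ = d² × 15 / v. With d = 0.64 this is 6.144 / v, on 58 df (change) or 57 df (ANCOVA), two-sided alpha 0.05. The d of 0.64 is the effect the Sample Size section cites from a trial in infants aged 6–12 months. It is taken here as scaled by the cross-sectional SD, which is an assumption.

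| Assumed ρ | v, change | v, ANCOVA | Ratio | 60 / ratio (families) | Power, change | Power, ANCOVA |
|---|---|---|---|---|---|---|
| 0.3 | 1.40 | 0.91 | 0.65 | 92 | 0.54 | 0.72 |
| 0.5 | 1.00 | 0.75 | 0.75 | 80 | 0.68 | 0.80 |
| 0.7 | 0.60 | 0.51 | 0.85 | 71 | 0.88 | 0.93 |
| 0.9 | 0.20 | 0.19 | 0.95 | 63 | 1.00 | 1.00 |

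Simulation (4,000 runs per row) gave 0.54 v 0.73, 0.67 v 0.79 and 0.88 v 0.92 for the first three rows. A comparison of 7-month values that ignores baseline has v = 1 and power 0.68. The change score is therefore no better than ignoring baseline at ρ = 0.5, and worse below it.

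**The document's nearest figure.** Table 2 gives a 3-week test–retest range of 0.82–0.95 across several sleep items, including night wakings. If that held over two months, the ratio would be (1 + 0.82)/2 = 0.91 to (1 + 0.95)/2 = 0.975, a variance saving of 9% down to 2.5%.

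**Chance imbalance.** Given a baseline difference b between arms, the change-score estimate shifts by −(1 − ρ)b. The ANCOVA estimate does not shift. The standard error of b is √(2/30) = 0.26 SD. At ρ = 0.5, a one-standard-error imbalance moves the change-score estimate by 0.5 × 0.26 = 0.13 SD, against a target of 0.64 SD. At ρ = 0.9 the shift is 0.1 × 0.26 = 0.03 SD.

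**The case against.** The strongest reply is that nothing here is wrong: the Abstract defines the outcome as change, and the planned test estimates change in a randomised comparison with a pre-randomisation baseline. That stands. A reader might infer that the RM-ANOVA is biased or invalid. It is not, because it controls type I error and is unbiased over randomisations.

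A reader might also infer that selecting infants with poor sleep biases the comparison through regression to the mean. The document does not support that. Regression acts on both arms alike in expectation and matters only through chance imbalance, which is counted above. Nor does varied entry ("have an infant who has greater than 3 night wakings per night and/or is awake greater than 60 min during the night", or short total sleep) favour ANCOVA in itself: stable differences between infants raise ρ and shrink its advantage.

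The size of the gain is also open to challenge, and this largely stands:

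- The document gives no 5-to-7-month correlation. A two-month value in rapidly developing infants is plausibly lower than a 3-week retest, but that is a judgement.
- The ratio (1 + ρ)/2 needs equal variances. With a 7-month to baseline SD ratio k, it becomes k²(1 − ρ²)/(k² + 1 − 2ρk). At ρ = 0.5 this is 0.94 for k = 1.4 and 0.47 for k = 0.7. The direction holds but the figure moves.
- If d = 0.64 was scaled by the SD of change, change-score power is 0.68 whatever ρ is.
- Power is computed at 0.05, while the plan mentions a Bonferroni correction without stating its scope.

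**Conclusion.** This is an improvement in efficiency, not the repair of an invalid test. For large samples ANCOVA has the smaller variance at every ρ below 1 when variances are equal, and it removes the over-correction of chance imbalance.

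The size depends on ρ. The saving is 35%, 25%, 15% and 5% of the change-score variance at assumed ρ of 0.3, 0.5, 0.7 and 0.9. The matching power gains at d = 0.64 are 18, 12 and 5 percentage points at the first three values and negligible at 0.9. These rest on equal variances, cross-sectional scaling of d, 30 per arm and two-sided alpha 0.05. It would go too far to conclude that the trial is underpowered or loses any one fixed number of families, because the document does not give the correlation that would settle this.

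Adjustment also reconciles the two wordings of the outcome. With baseline in the model, the arm coefficient is the same whether the response is change or 7-month wakings.

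**What to change.** By a dated amendment made before any results by arm are seen, make the primary analysis an ANCOVA of 7-month night wakings on arm plus baseline night wakings, in all randomised families. An equivalent mixed model that constrains the baseline means to be equal would also serve. Report the adjusted mean difference with a 95% CI.

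State in the amendment how the two parental reports enter: either averaged within family, or modelled jointly with a family-level random effect. Do the same for nocturnal wakefulness and longest sleep episode. Keep RM-ANOVA as a sensitivity analysis.

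The cost is about one residual degree of freedom and the amendment, with no new data or software. Timing matters. The Trial Status note reports 54 triads already enrolled, and the Phase 2 interviews sample families within each group by their observed change in wakings. The amendment should therefore precede any look at outcomes by group and should record what had been seen when it was made.
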